### Recruitment

Eligible women receive an invitation to participate and the written trial information by mail together with the invitation to the first midwife consultation. Oral information is given by the consulting midwife during the first midwife consultation (14 to 15 weeks of gestation). Written consent is given any time during the pregnancy and confirmed with the participant upon arrival at the delivery unit at the time of birth. Subsequently, consenting women are randomized. The flow of participants and the time schedule are illustrated in Figure 2.

**Figure 2 F2:**
[figure not shown]
**Time schedule and flow of participants.** GA, gestational age (weeks); *t*, time.

### Randomization

Randomization is computer-generated, with a 1:1 allocation to primary delivery of the anterior or posterior shoulder by a third party not otherwise involved in the trial. The allocation is concealed in 650 identical, opaque, sequentially numbered sealed envelopes. The allocation list is stored electronically by a third party not otherwise involved in the trial. Recruited women are randomized after confirmation of consent upon arrival at the delivery ward and a random allocation envelope is drawn. The envelope is opened by the midwife when the patient enters the second stage of labour and is destroyed thereafter. The allocation is only shown to the midwife and the assistant, and if necessary the obstetrician. During delivery, the midwife and assistant observe what shoulder is delivered first, and this is registered on the clinical registration form.

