### Data management

Data are recorded on clinical registration forms and entered into a SPSS database (SPSS Inc., Chicago, IL, USA) by the primary investigator. Data will be available only to the investigators and the data monitor. After completed follow-up, data will be cleaned and consecutively locked before the allocation is broken.

All clinical registration forms are identified by a coded ID number according to randomization, to maintain participant confidentiality. All study-related participant information is stored in a locked room at the study site. Lists linking participant ID numbers to personal identification numbers are stored separately. Trial data will be stored for 10 years. Data will subsequently be anonymized and personally identifiable information destroyed.

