### Statistics

An audit at a Danish University Hospital of all their primary vaginal deliveries from 2003 to 2011 (*n* = 15,587) found that 86% sustained a perineal tear [3]. The hypothesis of this trial is that primary delivery of the posterior shoulder can reduce the incidence of perineal tears, and that a reduction of 10% is clinically significant. It is assumed that the rate of perineal tears using the traditional method of delivering the anterior shoulder first is 85%. The sample size calculation for the primary outcome is based on a minimal relevant difference in the proportions of perineal tears between the two intervention groups of 10%, with 80% power and a significance level of 0.05. Thus, we estimated that 250 women would have to be included in each intervention arm. In Denmark, 18% of primiparous women had an acute Cesarean section in 2011 [20]. Because of this probability of acute Cesarean section and the likelihood of drop-outs, 650 women will be included in this trial.

At the University of Copenhagen, Holbæk Hospital, 840 children were delivered by primiparous women in 2011. With an inclusion rate of 80% and assessment starting in January 2013, it is estimated that randomization can be finalized before December 2014.

All included women delivering vaginally will be included in the final analysis. The analysis will primarily be based on an intention-to-treat principle. It will be supplemented with a per-protocol analysis (of the women who received their random allocation) and an as-treated analysis (according to how the shoulders were actually delivered). Categorical variables, including the primary outcome, will be analyzed with the chi-squared test or Fisher’s exact test as appropriate, and the odds ratios presented with 95% confidence intervals. Continuous variables will be assessed for normal distribution with the Kolmogorov-Smirnov test. When normally distributed, they will be analyzed with a *t* test, and when not, with a Mann-Whitney test.

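### Destroying the allocation envelope once the midwife has opened it removes the only physical proof of the allocation shown, and the remaining records may not reveal a second envelope or a wrongly copied number

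*Protocol article*

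**What the plan says.** The Randomization section describes the envelopes: "The allocation is concealed in 650 identical, opaque, sequentially numbered sealed envelopes". Drawing comes first: "Recruited women are randomized after confirmation of consent upon arrival at the delivery ward and a random allocation envelope is drawn". Opening comes later: "The envelope is opened by the midwife when the patient enters the second stage of labour and is destroyed thereafter". The contents are shown to the midwife and the assistant, and to the obstetrician if needed. Those two also note which shoulder came first and enter it on the registration form.

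Three records outlive the envelope:

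- The allocation list (Randomization): "The allocation list is stored electronically by a third party not otherwise involved in the trial".
- The form number (Data management): "All clinical registration forms are identified by a coded ID number according to randomization, to maintain participant confidentiality".
- The link to the woman (Data management): "Lists linking participant ID numbers to personal identification numbers are stored separately".

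The Interventions section makes the midwife responsible for delivering the shoulders, even when a physician performs a vacuum delivery, and has protocol deviations entered on the form. The Statistics section limits the final analysis to women who deliver vaginally and gives the expected loss to Caesarean section: "In Denmark, 18% of primiparous women had an acute Cesarean section in 2011".

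**The concern.** The midwife cannot be blinded. The Background describes anterior-first delivery as the textbook recommendation, and the Statistics section calls it the traditional method, so some preference among operators is plausible, although no passage reports one. Good practice is therefore to keep evidence of what each envelope contained and which woman it served. Here the stated rule disposes of that evidence straight after opening.

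Two things are at stake. If an unwelcome envelope were set aside and a second one used, the arm would be chosen by the operator in the light of second-stage circumstances, and the intention-to-treat comparison would carry that selection. Without any misconduct, a number copied wrongly onto the form could attach the wrong arm to a woman when the allocation is broken after data lock, and nothing would remain to settle which number was right.

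**Working it through.** **Step 1. The plan's own figures.** Inputs from the Statistics section: 85% against 75%, 80% power, significance level 0.05 (taken as two-sided; the article does not say).

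n per arm = [1.960 × √(2 × 0.80 × 0.20) + 0.842 × √(0.85 × 0.15 + 0.75 × 0.25)]² / 0.10²
= [1.960 × 0.5657 + 0.842 × 0.5612]² / 0.01 ≈ 250.

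This reproduces the stated 250 per arm. Two arms need 500, so 650 allows for 650 − 500 = 150 women (150/650 = 23.1%) lost to acute Caesarean section and drop-out together.

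**Step 2. Numbers without a vaginal birth.** Expected count = 650 × rate of Caesarean section after the envelope is drawn.

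| Rate | Source | Numbers without a vaginal birth |
|---|---|---|
| 5% | assumption | 32.5, about 33 |
| 10% | assumption | 65 |
| 18% | protocol, national, 2011 | 117 (leaving 533) |

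The count passes 100 only if the rate is at least 100/650 = 15.4%. The 18% describes Danish primiparous women. It may include sections performed before any envelope is drawn, which would lower the count, and it does not describe the eligible women with one previous Caesarean section.

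**Step 3. What the surviving records can show.**

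| Event | What the records would show |
|---|---|
| Midwife opens the assigned envelope but delivers the other shoulder first | The recorded shoulder disagrees with the list. Visible as non-adherence. |
| Second envelope taken, its method used, its number entered | Shoulder, form and list all agree. The woman looks compliant in the intention-to-treat, per-protocol and as-treated analyses. Visible only if the first number was tied to her when it was drawn. |
| Correct envelope used, number copied wrongly | The list returns the allocation of another number; at 1:1, about half of such errors would give the other arm. The result looks like non-adherence, which the protocol permits for spontaneous delivery or on safety grounds. A duplicate number, or a mismatch with no deviation registered, may raise a query, but no envelope remains to resolve it. |

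The last two rows turn on when the number is linked to the woman. The Data management section says that form numbers follow randomization and that a linkage list exists. It does not say whether the link is made at drawing, at opening or after delivery.

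**Step 4. Combining the steps.** Because the analysed set already lacks tens of numbers, and up to about 117 on the protocol's own rate, a few unexplained ones would not draw attention there. The documents give no basis for estimating how many swaps or errors occur, so no bias in the treatment effect can be calculated.

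**The case against.** A reader might infer that a swapped allocation could never be detected. The documents do not support that. An uninvolved third party keeps the list, forms carry a randomization-based number, numbers are linked to women, and the shoulder is recorded. A number without a vaginal birth can be checked against women who had a Caesarean section, and a discarded number would have no such woman. Women with a Caesarean section are absent from the analysed set but need not be gaps in the randomization record. Drawing also precedes opening, so a swap needs a second envelope, and the assistant sees the allocation too. This stands, and it limits the claim to evidence that is weaker, not absent.

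A reader might also take "a random allocation envelope is drawn" to mean that envelopes are picked out of order, contradicting their sequential numbering. The phrase can equally mean an envelope holding the random allocation, and the Statistics section uses the same two words for the assignment itself. It is ambiguous, not a contradiction. Even so, nothing in the section says that the next number is taken.

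A log of drawn numbers may exist in the full Danish protocol, which is not shown, so its absence here is not held against the plan. All midwives are trained in both methods, and no preference is documented. Destruction may have been meant to protect the blinding of assessors and the primary investigator; the article gives no reason.

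Destruction itself remains. It is a stated rule, not an omitted detail, and a box closed to those same people would protect blinding equally well.

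**Conclusion.** The point holds as a minor weakness in the audit trail. Destroying the opened envelope discards the only physical proof of the allocation shown, and the surviving records may miss a second envelope used under its own number or fail to resolve a copying error.

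The scale of the background against which stray numbers would have to be noticed is up to about 117 of 650 at the national 18%, or about 33 to 65 at an assumed 5-10%. The number of swaps or errors is unknown and no bias is shown. The conclusion rests on two assumptions: that the midwife who opens the envelope is the one who delivers the shoulders, which is how the Randomization and Interventions sections read together, and that no record tying number to woman is made at drawing beyond those the article describes. If such a record exists, a second envelope would be much easier to find, but a disputed number still could not be checked against its envelope.

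**What to change.** In the Randomization section:

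1. Replace the destruction rule with retention. Every envelope, opened or unopened, including those of women who have a Caesarean section, goes into a locked box held by the third party and closed to the outcome assessors and the primary investigator.
2. Have the third party reconcile all 650 envelopes with the allocation list and the registration forms before database lock.
3. Replace the ambiguous drawing phrase with a rule that the next envelope in numerical order is taken, and that the participant ID, date and time are written on it while it is still sealed.

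The cost is a pen entry per woman, a locked box and one reconciliation by a party who already holds the list. The article reports that recruitment is under way and that amendments need ethics committee acceptance, so the change would need that step. Envelopes already destroyed cannot be recovered; for those women, reconciliation would rest on the list, the forms and the linkage list.

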### Data management

Data are recorded on clinical registration forms and entered into a SPSS database (SPSS Inc., Chicago, IL, USA) by the primary investigator. Data will be available only to the investigators and the data monitor. After completed follow-up, data will be cleaned and consecutively locked before the allocation is broken.

All clinical registration forms are identified by a coded ID number according to randomization, to maintain participant confidentiality. All study-related participant information is stored in a locked room at the study site. Lists linking participant ID numbers to personal identification numbers are stored separately. Trial data will be stored for 10 years. Data will subsequently be anonymized and personally identifiable information destroyed.

### Data monitoring

The steering committee consists of the authors of the protocol and [name], Head Midwife, Department of Obstetrics and Gynaecology, University of Copenhagen, Holbæk Hospital.

To ensure that it is not unethical to continue due to one intervention causing markedly more perineal trauma, interim analyses will be performed by a data monitor not otherwise involved in the trial after the first year and consecutively every 6 months until the end of the trial. In the interim analysis, the distribution of the two interventions will be estimated among cases with no perineal tears and cases with third- and fourth-degree tears. The steering committee will be notified if more than 60% of the cases with no tears or a higher-degree tear belong to a particular intervention group. The steering committee will then decide if the trial has to be stopped before completion.

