**Figure 1 F1:**
[figure not shown]
Primary delivery of (A) anterior shoulder and (B) posterior shoulder.

All midwives are trained in the two interventions by the primary investigator (HW) to secure uniform use of the techniques. Training sessions include an introductory video of the two methods and practical training on a birthing phantom (MODEL-med ‘Sophie and her Mum Full Birth Obstetric Trainer’, Carnegie, Australia). All midwives are also trained in evaluation and classification of perineal tears using an e-learning programme (GynZone ApS, Aarhus, Denmark). Primary training sessions (*n* = 14) took place from February to November 2013, and additional sessions are held every second month during the course of the trial to train new midwives and update previously trained midwives. Attendance at a training session accredits midwifes to deliver included patients.

The participants can deliver in the position they prefer, and if spontaneous delivery of the shoulders occurs, this is to be respected regardless of randomization. If during delivery the midwife judges that an alternative method of delivery is preferred with regard to the safety of the birthing mother, this overrules randomization. Episiotomy may be used in accordance to local guidelines, as judged necessary by the midwife. In case of vacuum-assisted delivery, which according to guidelines is performed by physicians, the midwife delivers the shoulders. Any deviations from the protocol are registered on the clinical registration form.

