### Assessment

After delivery of the placenta, a blinded midwife or doctor not otherwise involved in the delivery assesses the perineum and grades the perineal tears. Tears are sutured and officially classified and coded independently of the trial by the midwife responsible for the delivery or a doctor according to the hospital guidelines. Secondary outcome measures are registered by the midwife responsible for the delivery. Assessors of the primary outcome and the primary investigator are blinded to randomization.

Registered third- and fourth-degree tears are validated through manual assessment of patient records. We assume that higher-degree tears, in particular, may be diagnosed after trial assessment during repair. In order not to underestimate the level of higher-degree tears, data on all third- and fourth-degree tears in our study population registered in the hospital register during the trial period will be retrieved after the end of the trial. These data will be validated against patient records and any additional confirmed cases of third- or fourth-degree tears in our study population will be incorporated into the final dataset.

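### Interim alerts by arm go to a steering committee that presumably includes the primary investigator, who is declared blind and trains the midwives, with no masking or exclusion stated

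*Protocol article*

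**What the plan says.** All references are to the protocol article.

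- **Data monitoring, who looks.** An outside person does the analysis: "interim analyses will be performed by a data monitor not otherwise involved in the trial after the first year and consecutively every 6 months". At each look "the distribution of the two interventions will be estimated among cases with no perineal tears and cases with third- and fourth-degree tears".
- **Data monitoring, who is told.** "The steering committee will be notified if more than 60% of the cases with no tears or a higher-degree tear belong to a particular" arm. The recipients are then identified: "The steering committee consists of the authors of the protocol and" the Head Midwife of the trial department. On stopping: "The steering committee will then decide if the trial has to be stopped before completion".
- **Assessment.** "Assessors of the primary outcome and the primary investigator are blinded to randomization".
- **Interventions (text after Figure 1).** The primary investigator trains all midwives in both techniques, and "additional sessions are held every second month during the course of the trial to train new midwives and update previously trained midwives". Midwives may depart from the allocation on safety grounds and may use episiotomy on their own judgement.
- **Randomization and Data management.** The delivering midwife and assistant see the allocation. The primary investigator enters the registration forms. After follow-up, "data will be cleaned and consecutively locked before the allocation is broken".

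**The concern.** A case with no tear is the complement of the primary outcome, any perineal trauma. An alert on the no-tear limb is therefore a comparative result on the primary endpoint, and an alert on the severe-tear limb is a comparative result on its most serious component. The plan gives the looks to someone outside the trial, which is sound, and then routes the result to the people who run it.

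If the committee decides to continue, the primary investigator may go on with training and data entry knowing which technique is ahead. Shoulder delivery cannot be masked from the midwife, and she keeps discretion over departures from allocation and over episiotomy. Emphasis in training, or informal word within a single unit, could then shift how the remaining births are conducted in the interim direction. Blinded grading of tears does not protect against a change in the conduct of the birth itself. The final report would also find it hard to state without qualification that the primary investigator was blind.

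**Working it through.** **1. The text side by side.** Assessment: the primary investigator is blind. Data monitoring: an arm-level imbalance goes to a committee of the protocol authors and the Head Midwife, who must act on it. The two fit together only if the alert hides the arms or the primary investigator does not receive it. Neither is stated.

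**2. How often would an alert occur?** The plan gives no figure for this, so there is none to reproduce. (The planned 250 per arm does reproduce, with a two-sided pooled test of 85% v 75% at 80% power, and is not at issue.)

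Inputs:
- No-tear rate: 1 − 0.85 = 15% (Statistics).
- Vaginal births: 650 × (1 − 0.18) = 533 (Statistics, drop-outs ignored).
- Look positions: assumed, because the plan gives calendar times only. One scenario has a look at half of 533 (267). The other has looks at one third and two thirds (178 and 355). A look at the last birth is left out, since no later births can be affected.
- Severe-tear rate: assumed 4 to 6%; the document gives none.
- Identical techniques, each case equally likely to come from either arm.

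**Rule for one limb.** With m cases, X ~ Binomial(m, 0.5), and the alert fires if X > 0.6m or m − X > 0.6m. The probability is then averaged over m ~ Binomial(births, rate).

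**One look at 267 births.**
- No-tear limb: 267 × 0.15 ≈ 40 cases expected. At exactly m = 40 the probability is 15.4%, and at m = 39 it is 20.0%, because an exact 24:16 split does not count as more than 60%. Averaged over m: 19.9%.
- Severe-tear limb at 4%: 267 × 0.04 ≈ 11 cases; averaged probability 48.9%.
- Severe-tear limb at 6%: 267 × 0.06 ≈ 16 cases; averaged probability 40.6%.
- Either limb, 4%: 1 − (1 − 0.199)(1 − 0.489) = 0.591.
- Either limb, 6%: 1 − (1 − 0.199)(1 − 0.406) = 0.524.

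An exact calculation that lets the two counts depend on each other gives the same values, 59.1% and 52.4%.

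**Looks at 178 and 355 births** (simulation, 200,000 trials):

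| Severe-tear rate | Alert at 178 | Alert at 355 | At least one |
|---|---|---|---|
| 4% | 69% | 51% | 79% |
| 6% | 64% | 43% | 73% |

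**3. Under the planned effect.** With 15% v 25% no tear, the expected share of no-tear cases in the better arm is 0.25 / (0.15 + 0.25) = 62.5%. The no-tear limb alone then fires about 64% of the time at 267 births.

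**The case against.** The strongest reply is that an aggregate notice is not unblinding in the sense that the plan uses. Blinding to randomization reads most naturally as not knowing each woman's allocation, and a notice of a split beyond 60:40 reveals no one's allocation. This stands in part. The disclosure is of aggregate results, and it weakens the purpose of the primary investigator's blinding without revealing any individual assignment.

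Several stronger readings are tempting, and the document does not support them:

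- **That the rule on breaking the allocation after lock is breached.** That sentence concerns linking the locked data to the allocation list. The data monitor must use allocation earlier in any case.
- **That the whole leadership is declared blind.** Only the outcome assessors and the primary investigator are.
- **That every recipient would know which arm is ahead.** The article does not say whether the notice names the arm, and the full protocol, which exists in Danish, may say. Still, the article itself fixes who receives the alert and who decides, and a decision to stop on ethical grounds invites asking for the direction.
- **That the same people train, enter and clean data, and manage the unit.** Training and data entry are assigned to the primary investigator. Who cleans the data is not stated. That the Head Midwife manages the delivering staff is inferred from the title, and that the primary investigator is an author is likewise an inference.

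Two further points have some force. The primary investigator already enters forms recording which shoulder came first, so this person's blinding is fragile anyway. That is a separate weakness and no reason to add a tabulated comparison. Also, an alert that fires this often without a true effect says little about the truth. But recipients may still act on a chance direction, and the plan gives them no alert frequency to calibrate by.

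**Conclusion.** The concern holds as a routing problem. The plan sends an arm-level result on the primary endpoint or on severe tears to a committee that presumably includes its declared-blind primary investigator, without masking or exclusion. The event is plausible: with identical techniques, about 52 to 59% for one look at 267 births and 73 to 79% for looks at 178 and 355.

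These figures rest on assumed look positions, an assumed severe-tear rate of 4 to 6%, and independent allocation of cases to arms. Much of the frequency comes from the severe-tear limb, whose rate the document does not give. The firmer figure is the no-tear limb alone, about 20% at 267 births, which uses the plan's own 15% but still an assumed look position.

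The size of any resulting bias cannot be estimated from the document, and no passage shows results reaching midwives or assessors. The case for change is that the exposure is avoidable at almost no cost.

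**What to change.** Amend the Data monitoring section as follows:

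- The existing data monitor reports any alert with coded arms (A/B) and a continue or stop recommendation to steering-committee members other than the primary investigator and the Head Midwife.
- Those two receive only continue or stop. Sending the message after every look would keep it from revealing that an alert occurred.
- Recipients are bound not to pass results on.

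Then reconcile Data monitoring with Assessment, so that the statement about the primary investigator's blinding is true after an alert as well as before one. If the full protocol already masks or restricts the alert, one sentence in the article saying so is enough.

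The cost is wording and a short instruction to the data monitor, with no extra women or analyses. The downside is that two members with local knowledge are absent from the stop or continue discussion, and arm identity may have to be revealed to the deciding members if stopping is considered. The document does not show how many remaining members are free of trial duties; the sponsor should check this before adopting the wording.
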